### Data integration and analysis

The data will provide ongoing information of intervention performance and implementation. The run charts and emergent findings of the process evaluation will be reviewed monthly with a full quarterly review by the research team and every 6 months by the advisory board to identify areas for refining or boosting intervention components to maximise the programme effects. The target performance for the intervention for the final observation will be achieving a minimum of 30% of women (from intervention exposed practices) achieving the following PPC objectives:HbA1c ≤ 48 mmol/mol (6.5%)Prescription of 5 mg folic acid pre-pregnancyCessation of potentially teratogenic therapies

Practice level performance will also be monitored considering the proportion of women:Having a reproductive review and care plan instigatedEngaged in the pre-pregnancy care pathway—referred to intermediate or hospital diabetes teamsCommencing on folic acid 5 mgInstigated on contraceptionHbA1c testing and results

The extracted data will be imported into SPSS v26 and checked for accuracy (missing data or errors). The primary analysis will be based on collating the collective outcome and performance data from all the participating practices into run charts and performance metrics. In terms of PPC criteria, baseline performance will be established and then we will monitor performance prospectively (four-monthly intervals), to establish progression in performance as percentages to the final 30% target.

Hence, we will be able to provide a robust estimate of intervention effects and costs. We will also be able to compare the antenatal and pregnancy outcome data from the intervention practices to the non-participating practices to establish estimate differences in performance for the main performance measures and pregnancy outcomes. We will also consider practice level variations in process performance.

We will also report pregnancy interventions (initiation of additional hypoglycaemic agents) and birth outcomes (macrosomia, shoulder dystocia, caesarean rates, neonatal admissions, postnatal length of stay and other adverse outcomes); comparing practices exposed and not exposed to the PREPARED interventions. The process evaluation data will provide insights into cultural, interactional, and behavioural changes in relation to women and health professionals. These data will help us consider whether the intervention has changed the way care is delivered and how it is experienced by women with T2DM.

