### Study design

A multimethod design will be used, with a clinical audit of PPC related processes and outcomes; and an integrated process evaluation informing intervention feasibility, implementation, and behaviour change; and an economic cost consequences analysis. The clinical audit will provide PPC performance data. Following CAS theory, we will use frequent repeat measures of the PPC performance metrics to monitor the delivery and impact of the intervention components at four-monthly intervals over 18 months from baseline (performance 12 months pre-intervention). At each timepoint performance measures will be reviewed to inform where intervention effects might need boosting or refining. The target performance for the intervention will be a minimum improvement of 30% at final observation in the proportion of women meeting current NICE pregnancy criteria [17]. Practice level performance will also be monitored considering the number of women: having a reproductive review; accessing PPC; receiving folic acid 5 mg; and instigated on contraception. Table 1 provides an overview of the data that will be used to determine systemic (across the exposed practices) and practice level performance (see Table 1). The PPC and pregnancy outcomes will have a relatively low incidence at the practice level so these will only be considered at the systemic level.

**Table 1 Tab1:** Performance measures

Performance measures	Systemic Performance	Practice Performance
Process data		
• Reproductive review and care plan instigated	Yes	Yes
• Care pathway activation	Yes	Yes
• Initiation of folic acid 5 mg	Yes	Yes
• Contraception advise given	Yes	Yes
• Instigated on contraception	Yes	Yes
• HbA1c testing and results	Yes	Yes
Pre-pregnancy care targets		
• HbA1c ≤ 48 mmol/mol (6.5%)	Yes	No
• Prescription of 5 mg folic acid pre-pregnancy	Yes	No
• Cessation of potentially teratogenic therapies	Yes	No
Pregnancy outcomes		
• Neonatal hypoglycaemia	Yes	No
• Macrosomia (birth weight > 4.5 kg)	Yes	No
• Shoulder dystocia	Yes	No
• Caesarean section incidence	Yes	No
• Neonatal intensive care admissions	Yes	No
• Postnatal length of stay	Yes	No
• Any other adverse outcomes	Yes	No

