### Study setting, sample size and participants

The study will take place in South London where currently a high proportion of women with T2DM become pregnant without effective PPC [3]. We will recruit 30 general practices for intervention exposure. Practices will be considered for inclusion if they have ≥ 25 women with T2DM of reproductive age (18–45 years), this will provide a pooled sample of 750 women. Two local hospital diabetes pregnancy services responsible for the maternity care of 80–100 women with T2DM per year from this area will also participate, so that pregnancy outcomes can be studied.

It is difficult to predict how many women will be actively trying to conceive during the study period (this will be an important finding in itself), but we have estimated based on the number of annual pregnancies reported there will be 120–150 pregnancies in the participating boroughs: with 40–50 pregnancies in the women attending the PREPARED exposed practices. If we assume that women will be trying for pregnancies for 12 months prior to conception, then we can further estimate that > 100 women will be requiring PPC intervention with the remaining women (*n* =  > 650) requiring reproductive review and contraception.

There are high levels of deprivation and ethnic diversity in the local area, hence, establishing intervention reach into these communities is an important objective for the study as these groups of women form a major proportion of the target population.

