### Data collection

The audit data (see Table 1) will be extracted from participating practices using an electronic template that we will install in the participating practices electronic record keeping system, the data collected will identify: women of child bearing age (< 45 years) attending appointments; reproductive assessments (activated on template); glycaemic control; changes to medications or contraception; PPC care-plan initiation; and PPC education or the dispensing of the integrated PREPARED self-help resources (leaflets and web-links). The pregnancy and pregnancy outcome data will be collected from the participating hospital audit systems which routinely collect these data for all women with diabetes as part of an ongoing national audit. The pregnancy booking data includes: glycaemic control; folic acid (5 mg) adherence; the prescription of any teratogenic therapies; and estimated pre-pregnancy weight. The birth outcome data includes: term and status of infant at birth including details of adverse outcomes; mode of birth; breast feeding status; maternal health/injury and depression; pregnancy complications; length of hospital stay; and neonatal care admissions. We will collect these data on all births during the observation period so we can compare outcomes in women from the intervention practices to unexposed practices. The hospital and practice level data will be extracted at baseline (12-month pre-PREPARED exposure) and then monthly to generate run charts monitoring process and outcome performance, with a full audit and review each quarter. The monthly data extractions will be continuous throughout the observation period (18 months). All data will be anonymised at source by hospital/practice administrators, practice codes will allow us to link them to the hospital data.

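### The 30% target does not fix its denominator, and the only population it names (women from exposed practices) would cap the result near 13% on the protocol's own figures

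*Protocol article*

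**What the plan says.** All references are to the protocol article.

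- **Data integration and analysis** sets the final target as "achieving a minimum of 30% of women (from intervention exposed practices") meeting three PPC objectives: HbA1c at or below 48 mmol/mol, 5 mg folic acid prescribed before pregnancy, and cessation of potentially teratogenic therapies. No other section names a population for the target.
- **Study design** words the target as "a minimum improvement of 30% at final observation in the proportion of women meeting current NICE pregnancy criteria", again without a denominator.
- **Study setting, sample size and participants** states "We will recruit 30 general practices for intervention exposure", each with at least 25 eligible women, and "this will provide a pooled sample of 750 women". It expects more than 100 of them to need PPC. The remainder, more than 650, are described as "requiring reproductive review and contraception".
- **Table 1** lists "Prescription of 5 mg folic acid pre-pregnancy" as a PPC target, separately from the process measure of starting folic acid.
- **Data collection** says the hospital booking record holds glycaemic control, "folic acid (5 mg) adherence; the prescription of any teratogenic therapies".

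**The concern.** The target is a threshold for a percentage, so its meaning depends on who is in the denominator. The only population named is women from exposed practices. The sample size section says most of those women need contraception, not preparation for pregnancy. A composite that includes pre-pregnancy folic acid is not one they would be expected to meet. Followed literally, a programme that worked well in the women it is meant for could still miss its target by a wide margin.

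This matters because the percentage is tracked at four-monthly intervals and the reviews decide which components to refine or boost. The Discussion also makes reaching the target the condition for having an implementable programme. The article itself states the target, its population and its components, so this is not a detail left to a fuller document.

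The third component has a related wording problem. A woman who never took a teratogenic medicine cannot cease one, so on a literal reading she could be scored as a failure.

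**Working it through.** **1. The plan's own figures.**
- Pool: 30 practices × 25 women = 750. Reproduces.
- Split: 100 + 650 = 750. Reproduces.
- Pregnancies in the boroughs: 80 to 100 per year × 1.5 years = 120 to 150. Reproduces, and implies that the 40 to 50 in exposed practices (one third of that) is an 18-month count.
- More than 100 women needing PPC: with 12 months of trying before conception and 18 months of observation, women trying at some point = annual pregnancies × (18 + 12)/12 = annual pregnancies × 2.5. This gives 100 to 125 only if 40 to 50 is an annual count. If it is an 18-month count, the result is 67 to 83.

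**2. Successes needed for 30%, by denominator.**

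| Denominator | Size | Successes needed |
|---|---|---|
| All women in exposed practices | 750 | 225 |
| Women needing PPC | 100 | 30 |
| Pregnancies in exposed practices | 40 to 50 | 12 to 15 |

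**3. Ceiling on the literal reading.** If only about 100 women can meet all three objectives:
- maximum = 100/750 = 13.3%
- 30% success among those women would show as 30/750 = 4.0%
- reaching 225 would need 225 − 100 = 125 of the other 650 women (19%) to meet pre-pregnancy criteria.

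**4. Sensitivity of the ceiling.** The Abstract gives 80 to 100 pregnancies for the exposed practices, the Methods 40 to 50, and the period is not always clear. Using annual rate × 2.5, divided by 750:

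| Pregnancy figure taken | Women needing PPC | Ceiling |
|---|---|---|
| 40 to 50 in 18 months | 67 to 83 | 8.9% to 11.1% |
| 40 to 50 per year | 100 to 125 | 13.3% to 16.7% |
| 80 to 100 in 18 months | 133 to 167 | 17.8% to 22.2% |
| 80 to 100 per year | 200 to 250 | 26.7% to 33.3% |

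Only the last row reaches 30%. At its upper end, 225 of 250 women needing PPC (90%) would have to succeed. It also credits the exposed practices with what the Methods give as the two hospitals' whole annual caseload.

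**5. Text that fits a pregnancy denominator.**
- The folic acid item is tied to pregnancy and kept apart from the process measure.
- Study design calls PPC outcomes low in incidence at practice level, and so assesses them only across practices.
- All three items are recorded at hospital booking.
- Data integration and analysis compares exposed with non-participating practices using antenatal and outcome data. The practice template is installed only in participating practices, so that comparison must rest on hospital records.

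**6. Precision with pregnancies as denominator.** The 95% Wilson interval for 12/40 is about 18% to 45%, and for 15/50 about 19% to 44%. Eighteen months hold 18/4 = 4.5 four-monthly periods, so an 18-month total of 40 to 50 gives about 9 to 11 pregnancies per review, of which 30% is about 3.

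**The case against.** The strongest reply is that the article never says all women. The parenthesis may only separate exposed practices from non-participating ones, and the data flow in step 5 already points to pregnancies. This stands. It means the literal denominator may not be the intended one, but it leaves the text without a stated one.

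It is also fair that the ceiling is conditional and that more than 100 is a lower bound. The range in step 4 reflects this.

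The study is an optimisation exercise reported by run charts and percentages, with no test stated against the target. That limits the consequence, but the target still steers the reviews and the conclusion.

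A reader might infer three stronger claims that the article does not support:
- **That the published 10% is the study's baseline and is not comparable with the target.** The 10% is a background figure. The study measures its own baseline over the 12 months before exposure, from the same systems, and this would be comparable if the same denominator were used.
- **That a cessation criterion excludes 84% to 88% of women.** The cited UK study's 16% and 12.2% are exposure rates. The unexposed remainder can include women who stopped in time as well as never-users, so the share excluded cannot be derived.
- **That the percentage must fall as contraception uptake rises.** With a fixed all-women denominator, it falls only if women who would have met the composite take up contraception instead.

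The difference between folic acid prescription in the target and adherence in the booking field is, on its own, operational detail that an article may leave to the full protocol. It matters here only because one source should serve every comparison.

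**Conclusion.** The point holds in a limited form: the denominator of the main target is not fixed, and the only population named does not work with the sample size section. On the Methods figures the ceiling is about 13%, with a range of about 9% to 33% across the protocol's pregnancy figures. This assumes that all women in exposed practices are counted, that the three objectives must be met jointly, and that essentially no woman outside the PPC group qualifies.

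It would go too far to call the target unattainable without those conditions. With women needing PPC or pregnancies as denominator, 30 of 100 or 12 to 15 of 40 to 50 is arithmetically possible. The spread between those counts and 225 of 750 is why the passages need reconciling.

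**What to change.** - State that the target denominator is pregnancies booked at the two participating hospitals in women from exposed practices. The practice codes already planned for linkage make this possible.
- Take all three criteria from the same booking fields in the 12-month baseline, at follow-up and in unexposed practices, and match the folic acid wording to the field used.
- Word the third criterion, as an outcome definition, as not being prescribed a potentially teratogenic therapy. This agrees with the Background, which describes the guideline item as avoidance and the cited study's definition as not taking such medicines. Never-users then do not count as failures.
- Keep all eligible women in exposed practices as denominator for process measures only, such as reproductive review.
- Reconcile the two pregnancy counts and give the period each covers.

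The change is to wording, since the booking data are already collected. The cost is precision: about 40 to 50 pregnancies, an interval of roughly 18% to 45% around 30%, and about 3 expected successes per four-monthly review, too few to guide boosting decisions without the process measures. Women identified as planning pregnancy would be a reasonable alternative denominator (about 100, so 30 needed), but the practice template is not installed in unexposed practices, so the comparison with them would be lost for this measure.

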### Intervention optimisation

At the end of the study, we will be able to assess how each component of the PREPARED intervention was refined during the study and their relative contributions to PPC performance. Based on this analysis, together with the findings of the process evaluation, we will revise the PREPARED programme. The revised programme will be presented at a stakeholder event bringing together women with T2DM, health professionals (primary care, diabetes, and maternal health) and service administrators, managers, and commissioners.

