## Development of PREPARED

The PREPARED programme is comprised of an integrated portfolio of interventions developed following the Medical Research Council (MRC) complex interventions framework [24], based on preliminary theory and modelling work that included: a systematic review of previous interventions [25]; a meta-synthesis of women’s experiences of PPC [26]; and a qualitative study with women with T2DM (*n* = 30) and health professionals (*n*= 22) exploring experiences of PPC and how to improve PPC uptake [15, 27]. The data from this work were used to develop a logic model mapping the key factors that mediate PPC uptake in relation to the women, health professionals and the care system. The intervention components were then integrated into the model targeting different mediating factors (see Fig. 1). As many of the mediating factors were behavioural or related to care systems, we also modelled the programme using: the COM-B (capability, opportunity, motivation to perform a behaviour) and the Behaviour Change Wheel (BCW) frameworks [28]; and Normalisation Process Theory [29, 30].

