**Fig. 1 Fig1:**
[figure not shown]
Integrating areas of potential intervention

Throughout the development of the intervention, we have also been working with a group of women with T2DM who have experienced a diabetes pregnancy. Together with them and health professionals from primary care, diabetes services and maternity care we have built the PREPARED intervention, which is comprised of the following theoretically modelled components:decision support systems to prompt pregnancy review in primary care;an integrated primary care care-pathway for PPC linking to diabetes intermediate care teams, women’s health and maternity services;reproductive intention and pregnancy reviews with collaborative care-planning for all eligible women;materials for promoting pregnancy awareness in women with T2DM;web-based information resources for women;and performance monitoring with feedback to practices on PPC activity and pregnancy outcomes.

The most important feature of our approach is that it is centred in primary care where the women receive their routine diabetes management, rather than hospitals where most PPC is currently provided. PREPARED involves installing interventions to promote PPC within the electronic management systems of general practices in primary care, along with a training package for the practice team. In this paper we outline the protocol for a study which will aim to optimise the different components of the PREPARED intervention by assessing their impact on women’s access to PPC (or contraception) and pregnancy outcomes. The study will start in October 2021 and is funded by the UK government through the Health Services and Delivery Research programme of the National Institute of Health Research (NIHR131250).

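### The article promises each component's relative contribution to PPC performance, but the design as described cannot separate component effects on the PPC targets

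*Protocol article*

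**What the plan says.** Under Intervention optimisation, the Protocol article says that "we will be able to assess how each component of the PREPARED intervention was refined during the study and their relative contributions to PPC performance". The next sentence makes this analysis, alongside the process evaluation, the basis for revising the programme.

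The rest of the article describes the following design.

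- **One bundle.** Development of PREPARED: "The PREPARED programme is comprised of an integrated portfolio of interventions". Six components are then listed, and delivery is described as follows: "PREPARED involves installing interventions to promote PPC within the electronic management systems of general practices in primary care, along with a training package".
- **One kind of exposure.** Study setting, sample size and participants: "We will recruit 30 general practices for intervention exposure". The only quantitative between-group comparison (Data integration and analysis) is of exposed with non-participating practices.
- **Refinement guided by performance.** Study design: "At each timepoint performance measures will be reviewed to inform where intervention effects might need boosting or refining". Data integration and analysis adds monthly and quarterly reviews, and a six-monthly advisory board review, "to identify areas for refining or boosting intervention components to maximise the programme effects".
- **Pooled analysis.** Data integration and analysis: "The primary analysis will be based on collating the collective outcome and performance data from all the participating practices into run charts and performance metrics". Study design and Table 1 keep the three PPC targets (HbA1c, folic acid, teratogenic medicines) at systemic level and mark them No at practice level.

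**The concern.** To say how much each component contributed to an outcome, the components must differ in some way that is not tied to the outcome itself: between practices, between women, or over time. The article describes no such variation. Every exposed practice is offered the same portfolio, and what changes over time is guided by the performance data that would later be used to judge the change.

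At stake is what the study may conclude. If the revised programme gives more weight to one component because performance rose after that component was boosted, the reason may be the calendar, an earlier change, or a low interval followed by an ordinary one.

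**Working it through.** **The article's own figures.** 30 practices × 25 women = 750, which agrees with "this will provide a pooled sample of 750 women". Likewise 80–100 pregnancies a year × 1.5 years = 120–150, as stated for the boroughs. The article gives no figure for component effects, so the check is whether they can be identified at all.

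**Inputs from the article.** 30 practices; six listed components; a 12-month baseline and 18 months of observation; four-monthly performance points and monthly extractions; 40–50 pregnancies in exposed practices; more than 100 women estimated to need PPC.

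**Step 1: pooled four-monthly series.** Take points at baseline and at 4, 8, 12 and 16 months, with or without a final point at 18 months (5 or 6 points). The model has an intercept, a trend and six component indicators, so 1 + 1 + 6 = 8 columns. Each component indicator is 0 at baseline and 1 afterwards, so the six are the same column. The rank is 1 + 1 + 1 = 3: one combined effect can be estimated, not six.

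**Step 2: practice by month.** 30 practices × 30 months = 900 rows. Columns: 30 practice terms + 1 trend + 6 components = 37. The rank is 30 + 1 + 1 = 32. The six component effects again reduce to one. So even practice-level data would not separate components coded by what is offered.

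**Step 3: refinements at common dates.** Use six period indicators (baseline, and follow-up cut at 0, 4, 8, 12 and 16 months). Add five step terms for changes made in all practices at those cut points. The rank is 6 before and 6 after, so the steps cannot be told apart from period effects. This assumes simultaneous refinement, which the article does not state. If practices changed at different times, there would be contrasts, but with timing guided by performance or local circumstances they would be confounded.

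**Step 4: delivered, not merely offered.** Steps 1 to 3 concern what practices are given. Data collection and the process-evaluation audit also record what was delivered, and this will vary by woman, practice and month. Associations can therefore be computed. They are not component effects, because engaged practices and motivated women are likely to have both more delivery and better outcomes. They also fall mainly on process measures, since the PPC targets are not analysed by practice.

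**Step 5: regression to the mean.** Assumptions not in the article: a constant true rate, a refinement with no effect, a refinement triggered by an interval below the true rate, and independent successive intervals. True rates run from 10% (the current uptake given in Background) to 30% (the target).

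- 18 months ÷ 4 = 4.5 intervals; 40 ÷ 4.5 = 8.9 and 50 ÷ 4.5 = 11.1, so about 9–11 pregnancies per interval.
- Example with 10 pregnancies and a true rate of 10%: only an interval with no successes lies below the rate, and the next interval is expected at 10%. The apparent rise is 10 percentage points.
- Simulation over 9–11 pregnancies and true rates of 10%, 20% and 30%: apparent rise of 5 to 15 points.
- With 100 women per interval: 2.6, 3.5 and 3.9 points. If the same women are counted in successive intervals, independence fails and the artefact would be smaller.

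**The case against.** The strongest reply is that offering a component is not delivering it. The unit of observation is the patient-level care event, the template records individual actions, component use is audited quarterly, and inter-practice differences are to be examined. Table 1 keeps reproductive review, pathway activation, folic acid initiation, contraception, and HbA1c testing and results at practice level. PPC performance is not defined as the three targets alone, so the claim could be read as partly about processes. This stands. A reader might infer that no component contrast and no between-practice variation exist at all; the article does not support that. What exists is confounded and descriptive.

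Four further points stand in part.

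- Full, simultaneous delivery is inferred from a condensed article whose flowchart is not shown. Nothing in the text contradicts it.
- Low performance is not the sole stated trigger for refinement; emergent process-evaluation findings also count. Regression to the mean is therefore possible, not established.
- A reader might take 40–50 pregnancies as the denominator for PPC performance. The article does not settle this: the target is worded for women from exposed practices, and more than 100 are expected to need PPC.
- Iterative optimisation is a deliberate and explained choice. It is not challenged here. Releasing refinements in random order would alter that choice and would compare refinements, not components, so it is not recommended.

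The reply that the analysis plan will deal with this does not stand. The fault is a positive claim in the text, and no later choice of model creates contrasts that the described design lacks.

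**Conclusion.** The claim of relative contributions goes further than the described design allows. Separable effects of individual components on the three PPC targets cannot be identified: under common delivery, six effects reduce to one. A change after a refinement cannot be attributed to it, and chance alone could produce an apparent rise of about 5–15 points at 9–11 pregnancies per interval, or 3–4 points at 100 women, under the Step 5 assumptions. The rank result assumes that all practices receive the whole bundle together.

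The limits matter. The first half of the sentence, on how components were refined, can be supported from process data. The systemic estimate concerns the whole programme and is not touched by this point. A reader might also infer that the NHS implementation plan rests on these contributions, or that components will be dropped because of them. The article says only that the revision draws on this analysis together with the process evaluation, followed by a stakeholder event.

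**What to change.** Restate the sentence under Intervention optimisation in three parts:

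1. Quantitative impact on the PPC targets is claimed for the whole programme only.
2. Component contributions are appraised descriptively, from recorded delivery, practice-level process measures and qualitative data, and are not presented as separate effects.
3. The programme revision is said to rest on that descriptive appraisal.

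Keep a dated log of each refinement by practice, with the reason for it, so that the description can be set against the run charts.

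The cost is one reworded claim and a simple log. The design, sample, data collection and iterative approach stay as they are.
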